## Abstract

**Introduction::**

A herbal formula, Galgeun-tang-ga-cheongung-sinyi (GGTCS), is traditionally used for the treatment of rhinosinusitis in East Asian countries. However, there is a dearth of clinical evidence supporting the effects of this medication. Here, we describe the protocol for a randomized controlled study designed to investigate the efficacy and safety of GGTCS for the treatment of chronic rhinosinusitis (CRS).

**Methods and analysis::**

To investigate the clinical efficacy and safety of GGTCS for the treatment of CRS, a randomized, double-blind, placebo-controlled, parallel group, clinical trial has been designed. A total of 58 participants with CRS will be recruited and randomly allocated to a GGTCS or placebo group in a 1:1 ratio. The participants will be administered GGTCS or placebo granules 3 times a day for 8 weeks. Data will be collected from the participants at baseline and at 1, 2, 4, and 8 weeks after random allocation. The primary outcome measure will be the mean change in the Sino-Nasal Outcome Test-22 score from baseline to 8 weeks. The secondary outcomes will include the Total Nasal Symptom Score, EuroQoL 5 Dimensions 5 Levels score, Nasal Endoscopy Index, Lund-Mackay score, and total serum immunoglobulin E level.

**Discussion::**

The key elements for conducting a high-quality randomized clinical trial have been addressed in this protocol. In summary, the findings of this study are expected to provide a base for large-scale randomized controlled trials to confirm the safety and efficacy of GGTCS for the treatment of CRS and may consequently serve to improve future treatment strategies for this condition.

**Trial registration:** This study has been registered at the Korean National Clinical Trial Registry, Clinical Research Information Service (KCT0002835).

## Introduction

1

Chronic rhinosinusitis (CRS) is defined as a disease characterized by inflammation of the nasal and paranasal sinus mucosa that persists for more than 12 weeks.^[1]^ CRS is one of the most common chronic diseases, affecting 11.8% to 17.4% of the American population^[2]^ and 10.9% of the European population.^[3]^ This condition not only causes physical problems such as nasal congestion, thick mucus production, and loss of olfaction, but also impacts psychological wellbeing and daily functioning.^[4]^ Indeed, CRS is associated with a lifetime of medical and surgical resource consumption, resulting in significant health care expenditures; the range for overall CRS-related health care costs has been reported as $6.9 to $9.9 billion USD per year.^[5]^

CRS is a multifactorial disease with an elusive pathology; therefore, there are no specific targets for therapeutic interventions. Considering that it is an inflammatory disease, anti-inflammatory therapy including corticosteroids and antibiotics plays a role in its treatment. Although corticosteroids are known to be effective against nasal polyps, they can increase the risk of epistaxis.^[6,7]^ Moreover, antibiotics show limited treatment effects and are associated with gastrointestinal disturbances and allergic reactions such as skin irritation.^[8]^ In cases of marked mechanical obstruction of the airways or chronic disease that is unresponsive to maximal medical therapy, surgical intervention is the treatment of choice, although its effects are inconclusive.^[9]^

Because of the limited success of conventional therapy and the nature of the condition, herbal medicines are becoming increasingly popular and are frequently used by patients with rhinosinusitis in East Asian countries.^[10,11]^*Galgeun-tang* (GGT) is a herbal formula composed of 7 medicinal herbs (*Puerariae Radix*, *Ephedrae Herba*, *Cinnamomi Ramulus*, *Paeoniae Radix*, *Glycyrrhizae Radix et Rhizoma*, *Zingiberis Rhizoma Recens*, and *Zizyphi Fructus*). It has anti-inflammatory and immunoregulatory properties.^[12,13]^*Galgeun-tang-ga-cheongung-sinyi* (GGTCS, *Gegen-tang-jia-chuanxiong-xinyi* in Chinese, *Kakkon-to-ka-senkyu-shin’i* in Japanese) is a herbal prescription that is prepared by the addition of *Cnidii Rhizoma* and *Magnoliae Flos* to GGT and is also known to have anti-inflammatory effects.^[14]^ It is considered effective for otorhinolaryngological diseases^[15]^ and is used for the treatment of rhinosinusitis throughout East Asia.^[16]^

Despite the clinical experiences and experimental results supporting the use of GGTCS,^[14,15]^ few clinical trials have evaluated the effects of GGTCS for CRS. Here, we describe the protocol for a randomized controlled trial designed to assess the efficacy and safety of GGTCS for the treatment of CRS compared with placebo. This trial has been designed to better reflect the characteristics of traditional medicine by considering the traditional constitutional concept of GGTCS.

## Methods

2

### Objective

2.1

The aim of this study was to describe the protocol for a randomized controlled trial designed to clinically assess the efficacy and safety of GGTCS for the treatment of CRS.

### Study design and setting

2.2

This randomized, double-blind (patient, practitioner, and assessor), placebo-controlled, clinical trial will be conducted at the Woosuk Korean Medicine Medical Center in the Republic of Korea. The study period will include 8 weeks of medication and follow-up. The design is summarized in Fig. 1 and Table 1. The study protocol (version 1.1, 11 April 2018) follows the Standard Protocol Items: Recommendations for Interventional Trials (SPIRIT) guidelines (see Additional File 1).

**Figure 1 F1:**
[figure not shown]
Flowchart describing the study plan. GGTCS = Galgeun-tang-ga-cheongung-sinyi.

**Table 1 T1:**
[figure not shown]
Schedule of enrolment, interventions, and outcome measurements for a randomized controlled trial assessing the safety and efficacy of Galgeun-tang-ga-cheongung-sinyi, a herbal formula, for the treatment of chronic rhinosinusitis.

### Recruitment

2.3

Participant recruitment will begin in April 2018 at the Woosuk Korean Medicine Medical Center, and it is expected to be completed in December 2018. The trial will be advertised in local newspapers, public transportation, and the hospital, and a total of 58 participants will be recruited. Written informed consent will be obtained from all study participants before enrolment, and participants may decline to participate or withdraw at any time without disadvantage. The written informed consent form will include information on the background and purpose of the study, experimental and placebo drugs, outcome measures, and possible benefits and harms. The participants will be immediately notified when new facts regarding the study are found.

### Participant inclusion and exclusion criteria

2.4

#### Inclusion criteria

2.4.1

Participants will be considered eligible for inclusion if they meet the following criteria:

(1)Men or women aged 19 to 60 years at the screening visit;(2)A diagnosis of CRS based on the presence of rhinosinusitis symptoms for more than 12 weeks.A.Presence of more than 2 major symptoms or 1 major symptom with 2 minor symptoms:i.Major symptoms: facial pain/pressure, nasal obstruction/blockage, nasal discharge/purulence/discolored postnasal drainage, hyposmia/anosmia, purulence observed in the nasal cavity on examinationii.Minor symptoms: headache, fever, halitosis, fatigue, dental pain, cough, ear pain/pressure/fullnessB.A diagnosis of rhinosinusitis based on paranasal sinus computed tomography (CT) findings.(3)A Sino-Nasal Outcome Test-22 (SNOT-22) score of ≥ 20 at the screening visit(4)Ability to comprehend the purpose and process of the study as well as the properties of the investigational drug and voluntary provision of written informed consent

#### Exclusion criteria

2.4.2

The exclusion criteria will be as follows:

(1)A previous history of nose-related or allergy-related diseases and treatmentA.Nasal polyps, cystic fibrosis, primary ciliary dyskinesia, untreated deviated nasal septumB.Acute bacterial exacerbation of CRS (acute pain, acute pressure, fever, pus on discharge)C.Acute complication of CRS (abscess)D.Orbital or central nervous system complications of CRSE.Acute respiratory infection developed within the last 7 daysF.Use of topical decongestants or cromolyn sodium within the last 3 daysG.Use of antibiotics, antihistaminics, anticholinergics, and intranasal steroids within the last 1 weekH.Use of oral steroids or leukotriene receptor antagonists within the last 4 weeksI.Receipt of immunotherapy within the last 5 years(2)Presence of serious medical conditions that could interfere with clinical trial participationA.Uncontrolled hypertension (systolic blood pressure ≥ 160 mm Hg and diastolic blood pressure ≥ 100 mm Hg);B.Uncontrolled diabetes mellitus (HbA1c ≥ 6.5%);C.Abnormal kidney function test results showing blood creatinine levels that are more than twice the upper limit of the normal range;D.Abnormal liver function test results showing alanine aminotransferase or aspartate aminotransferase levels that are more than twice the upper limit of the normal range;E.Serious hyperlipidemia, anemia, active tuberculosis, thyroid disease, and other serious inflammatory and systemic diseases;F.Past or present history of malignant tumors.(3)Pregnancy, planning a pregnancy, or breastfeeding(4)Hypersensitivity to the investigational drug or any of its components(5)Participation in other clinical trials within the past 1 month(6)Communication difficulties that will not allow proper compliance with the investigator's instructions(7)Ineligibility for participation as judged by the investigator

At any time during the clinical trial, the participant may voluntarily withdraw from the clinical trial or also be discontinued at the researcher's discretion. If at any time during the clinical trial period, an adverse event (AE) determined to be harmful to the participant is observed, the researcher may temporarily discontinue the treatment of that participant. If continuing the trial is harmful to the participant based on the progression of the AE and its causal relationship with the drug, then the researcher will permanently discontinue the clinical treatment of that participant. Anyone who is discontinued early from the study due to an AE may receive the appropriate treatment for the AE, when necessary. Anyone who is discontinued early from the study owing to an AE must be assessed continuously by the researcher or someone designated by the researcher until the AE is resolved or is determined to be permanent.

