### Intervention

2.5

Participants will be randomly assigned to the GGTCS or placebo control group in a ratio of 1:1. They will receive treatment or evaluation according to the predetermined schedule. All participants will orally receive GGTCS or placebo 3 times a day 30 minutes before breakfast, lunch, and dinner or between meals for 8 weeks. The drugs for this clinical trial will be provided to the participants at baseline and at 1, 2, and 4 weeks after baseline. To confirm adherence to the medication regimen, participants will be requested to return unused drugs as well as spent wrappers of used drugs.

GGTCS consists of *Puerariae Radix*, *Ephedrae Herba*, *Cinnamomi Ramulus*, *Paeoniae Radix*, *Glycyrrhizae Radix et Rhizoma*, *Zingiberis Rhizoma Recens*, *Zizyphi Fructus*, *Cnidii Rhizoma*, and *Magnoliae Flos*. All constituents of this formulation comply with Korean Pharmacopoeia standards. The placebo will comprise corn starch, lactose hydrate, citric acid hydrate, ginseng flavored powder, and caramel coloring. Both drugs will be identical in appearance and color (brown) and will be packaged in identical white, opaque wrappers. The detailed components of GGTCS are described in Table 2. Both GGTCS and the placebo are manufactured by Hanpoong Pharm. Co., Ltd. (Wanju, Republic of Korea) according to good manufacturing practice standards. Quality control and quality assurance for quality and safety testing, packaging, and contents of the treatment drug, including checks for potential contaminants such as heavy metals or steroids, will be undertaken by the manufacturers to ensure drug stability and quality.

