### Safety and adverse events

2.11

For the safety of the study participants, complete blood cell counts, liver function tests, lipid tests, and urine analyses will be performed during the screening phase and at the end of the trial. Vital signs will be examined at every visit. Contact information for AE reporting at any time will be provided to all participants.

AEs associated with GGTCS have not yet been revealed. However, it is assumed that pseudoaldosteronism, myopathy, rash, pruritus, anorexia, gastric discomfort, nausea, diarrhea, autonomic dysfunction, and voiding dysfunction can occur in association with the individual herbal components of GGTCS. Any AE reported by participants will be recorded in the “Adverse Event Record Table.” A causal relationship between the event and GGTCS or placebo treatment will be evaluated using a 6-point scale: 1, definitely related; 2, probably related; 3, possibly related; 4, probably not related; 5, definitely not related; and 6, unknown. The seriousness of AEs will be scored using a 3-point scale: 1, mild; 2, moderate; and 3, severe. Any AEs will be reported in accordance with the regulations of the institutional review board (IRB).

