GGT is usually prescribed to Tae-eum type patients classified according to the Sasang constitutional medicine (SCM) theory, which is a Korean traditional medicine theory that categorizes humans into 4 distinct constitutions: Tae-yang, Tae-eum, So-yang, and So-eum. According to this theory, each type shows different sensitivities to some types of herbs and medicines.^[32]^*Puerariae Radix*, *Ephedrae Herba,* which are main ingredients of GGTCS, are known as medicinal herb for Tae-eum type patients. Assuming that the type and frequency of AEs caused by GGTCS for CRS treatment will differ among SCM types, we will use the KS-15 questionnaire in the present study to derive results that can serve a reference for planning future large-scale clinical trials reflecting the characteristics of traditional medicine.

The key elements for conducting a high-quality randomized clinical trial have been addressed in this protocol. In summary, the findings of this study are expected to provide a base for large-scale randomized controlled trials to confirm the safety and efficacy of GGTCS for the treatment of CRS and may consequently serve to improve future treatment strategies for this condition.

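### Exclusion (2)A requires both blood pressure limits to be exceeded, so a person over only one of them is left to investigator discretion

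*Protocol article*

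**What the plan says.** Section 2.4.2 (Exclusion criteria), item (2)A, excludes "Uncontrolled hypertension (systolic blood pressure ≥ 160 mm Hg and diastolic blood pressure ≥ 100 mm Hg". The parenthesis supplies the only numerical definition of uncontrolled hypertension in the article.

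Item (2)D of the same list, on liver function, uses *or*: "alanine aminotransferase or aspartate aminotransferase levels that are more than twice the upper limit of the normal range". Either enzyme alone is enough there. The list closes with a general discretionary item, (7): "Ineligibility for participation as judged by the investigator".

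Section 2.5 (Intervention) lists Ephedrae Herba and Glycyrrhizae Radix et Rhizoma among the constituents and has the granules taken three times a day for 8 weeks. The Discussion says of Puerariae Radix and Ephedrae Herba: "which are main ingredients of GGTCS". In section 2.11 (Safety and adverse events), "it is assumed that pseudoaldosteronism, myopathy, rash, pruritus, anorexia, gastric discomfort, nausea, diarrhea, autonomic dysfunction" and voiding dysfunction can occur because of individual components. For monitoring, the same section says: "Vital signs will be examined at every visit".

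**The concern.** A numerical exclusion limit exists so that entry does not depend on case-by-case judgement. With *and*, this one works only when both pressures are high. Someone with a very high systolic reading and a diastolic just under 100, or the reverse, passes the item although the heading describes them.

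The stake is participant safety, not inference. The protocol itself treats uncontrolled hypertension as a serious condition to be kept out. It anticipates pseudoaldosteronism, which as general medical knowledge raises blood pressure (the article does not say so). Section 2.11 also states that adverse events of the formula are not yet known, which argues for a firm entry limit over a discretionary one.

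**Working it through.** **Step 1. Apply the rule as written and with *or*.** The limits come from section 2.4.2; the readings are illustrative.

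| Reading (mm Hg) | Systolic ≥ 160 | Diastolic ≥ 100 | Excluded under *and* | Excluded under *or* |
|---|---|---|---|---|
| 190/95 | yes | no | no | yes |
| 150/115 | no | yes | no | yes |
| 165/105 | yes | yes | yes | yes |
| 150/95 | no | no | no | no |

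**Step 2. Look for another rule that catches the first two rows.** The heading of (2) concerns serious medical conditions in general. Item (2)E ends with other serious inflammatory and systemic diseases. Item (7) is investigator judgement. Section 2.11 has vital signs taken at every visit. The text after the criteria allows discontinuation at the researcher's discretion, and interruption or stopping once a harmful adverse event is seen. None states a blood pressure value.

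**Step 3. Gauge the size.** The article has no stated figure to reproduce and no blood pressure distribution. Means, SDs and correlations below are therefore assumptions, with bivariate normal screening values.

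Formulas, with S systolic and D diastolic:
- both = P(S ≥ 160 and D ≥ 100)
- either = P(S ≥ 160) + P(D ≥ 100) − both
- exactly one = either − both
- expected among 58 enrolled = 58 × exactly one / (1 − both), ignoring item (7)
- share caught by *and* = both / either

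Worked case, mean 130/84, SD 18/12, correlation 0.6: the limits lie (160 − 130)/18 = 1.667 and (100 − 84)/12 = 1.333 SDs above the means, so P(S ≥ 160) = 0.0478 and P(D ≥ 100) = 0.0912. The joint probability is 0.0219. Then either = 0.0478 + 0.0912 − 0.0219 = 0.1171, and exactly one = 0.0953 (from unrounded values). The expected number is 58 × 0.0953 / 0.9781 = 5.65, and the share caught is 0.0219 / 0.1171 = 0.19.

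| Mean (SD), mm Hg | Correlation | Both | Either | Exactly one | Expected of 58 | Share caught by *and* |
|---|---|---|---|---|---|---|
| 120/78 (14/10) | 0.6 | 0.0008 | 0.0153 | 0.0145 | 0.84 | 0.05 |
| 120/78 (14/10) | 0.8 | 0.0015 | 0.0146 | 0.0131 | 0.76 | 0.10 |
| 125/80 (16/11) | 0.6 | 0.0052 | 0.0437 | 0.0386 | 2.25 | 0.12 |
| 125/80 (16/11) | 0.8 | 0.0090 | 0.0399 | 0.0310 | 1.81 | 0.23 |
| 130/84 (18/12) | 0.6 | 0.0219 | 0.1171 | 0.0953 | 5.65 | 0.19 |
| 130/84 (18/12) | 0.8 | 0.0328 | 0.1062 | 0.0734 | 4.40 | 0.31 |

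**The case against.** The best counter-argument is that the list uses *and* loosely. Item (1)G joins four drug classes with *and*, and nobody would require use of all four before excluding. Item (2)E ends a list of alternatives the same way. On that view (2)A was meant as *either*, and its contrast with (2)D proves little. This stands as evidence about intent, but it does not rescue the rule: it shows that the same word carries two meanings in one list, so two people screening the same volunteer could decide differently.

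Second, a journal article may not match the operative eligibility form, and the full protocol (version 1.1) is not shown. How staff actually apply the item cannot be tested here. The printed criterion is nevertheless explicit; it is not a detail left out through condensation.

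Third, discretion and monitoring offer real protection. An investigator may well turn away someone at 190/95 under item (7). That reduces the practical risk without supplying the missing limit, and the provisions for harmful adverse events act only after treatment has begun.

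Fourth, the article does not list hypertension as an expected event or say that any constituent raises blood pressure, and the size estimate rests wholly on assumptions. Both are true. The upper end needs about 9% of volunteers at diastolic 100 or above, which nothing in the article supports. The logical gap in Step 1 depends on neither.

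**Conclusion.** The concern holds. As written, item (2)A does not exclude a person over only one of its two limits, and nothing else in the article sets a blood pressure limit. On the most charitable reading the item is ambiguous, and the literal reading is the less protective one.

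The number affected is uncertain and may be below one person: about 0.8 to 5.7 of 58 under the assumed distributions, before any discretionary exclusion. What is steadier across the scenarios is that *and* misses more than two thirds of the people over at least one limit. This is an eligibility and safety defect that should be corrected.

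**What to change.** Amend exclusion (2)A so that systolic pressure of at least 160 mm Hg *or* diastolic pressure of at least 100 mm Hg excludes. If the operative protocol or screening form already says *or*, the sponsor need only confirm this and correct the published wording.

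The cost is one word by amendment. Vital signs are already taken at every visit, so no new measurement is needed. Extra screen failures would be roughly 1 to 6 per 58 participants under the assumptions above.

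As a separate query while section 2.4 is open, the sponsor could confirm whether two or more major symptoms was intended in inclusion (2)A, which reads "Presence of more than 2 major symptoms or 1 major symptom with 2 minor symptoms". The article does not show what was meant, and nothing above depends on it.

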### Intervention

2.5

Participants will be randomly assigned to the GGTCS or placebo control group in a ratio of 1:1. They will receive treatment or evaluation according to the predetermined schedule. All participants will orally receive GGTCS or placebo 3 times a day 30 minutes before breakfast, lunch, and dinner or between meals for 8 weeks. The drugs for this clinical trial will be provided to the participants at baseline and at 1, 2, and 4 weeks after baseline. To confirm adherence to the medication regimen, participants will be requested to return unused drugs as well as spent wrappers of used drugs.

GGTCS consists of *Puerariae Radix*, *Ephedrae Herba*, *Cinnamomi Ramulus*, *Paeoniae Radix*, *Glycyrrhizae Radix et Rhizoma*, *Zingiberis Rhizoma Recens*, *Zizyphi Fructus*, *Cnidii Rhizoma*, and *Magnoliae Flos*. All constituents of this formulation comply with Korean Pharmacopoeia standards. The placebo will comprise corn starch, lactose hydrate, citric acid hydrate, ginseng flavored powder, and caramel coloring. Both drugs will be identical in appearance and color (brown) and will be packaged in identical white, opaque wrappers. The detailed components of GGTCS are described in Table 2. Both GGTCS and the placebo are manufactured by Hanpoong Pharm. Co., Ltd. (Wanju, Republic of Korea) according to good manufacturing practice standards. Quality control and quality assurance for quality and safety testing, packaging, and contents of the treatment drug, including checks for potential contaminants such as heavy metals or steroids, will be undertaken by the manufacturers to ensure drug stability and quality.

**Table 2 T2:**
[figure not shown]
Composition of the herbal formula Galgeun-tang-ga-cheongung-sinyi.

In principle, participants of both groups will be prohibited from concomitant use of any prescription and nonprescription medicines, functional health foods, or herbal medicines that can potentially affect the outcome of this experiment until after the follow-up period of 8 weeks. Participants who have been receiving medication for chronic diseases before initiation of this study will be allowed to continue their regimen, and care will be taken not to alter the dosage or type of drug.

